***2. Statistical Analysis***

**Primary Outcomes**

We will randomize 13 participants to each of the three study arms (control, 150 min∙wk^-1^, 300 min∙wk^-1^), to achieve 10 per group who complete the study (76% completion rate). Participants who have a cancer recurrence during the study will be excluded from the primary outcome analysis. The sample size is powered for the primary outcome biomarkers (sICAM-1 and sVICAM-1) with a hypothesis for a linear trend. The standard deviation of sICAM-1 and sVCAM-1 are 30 and 103 units, respectively. Against the hypothesis of a dose-response relationship with decreases of 22 and 44 units for low- and high-dose respectively for sICAM-1 and 74 and 148 units for sVCAM-1, 30 subjects provide 80% power for two, two-sided 0.025 tests (one for sICAM-1 and one for sVCAM-1, with the Type I error adjusted to maintain the experiment-wise error rate of 0.05). These reductions are consistent with prior exercise interventions in non-cancer survivorship populations, where clinically significant reductions in sICAM-1 and sVCAM-1 occur with 30 and 75 unit changes, respectively.[99-103]

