The feasibility of exercise will be quantified by comparing the proportion of participants in each group who achieve ≥80% of their prescribed exercise dose. The incidence of exercise dose-alteration will be quantified by comparing the proportion of participants who require a dose-reduction or cessation of exercise in each group. The indication for the dose-reduction or cessation will also be described qualitatively. As this aim intends to describe feasibility, we state no directional hypothesis. For the primary biomarker outcomes, we will use a linear mixed-effects regression to compare the change in biomarker levels for each group while controlling for other variables likely to influence sICAM-1 and sVCAM-1 (in addition to the effects from treatment group). Potential confounders (e.g., change in diet, sleep, or body weight) will be screened using univariate models; those that appear to be associated with the outcome will be entered sequentially in multivariate models. We will initially fit models including dose as a linear term, and assess model fit using standard methods. Alternatives to a linear dose trend include transformations of dose such as average actual dose, log-transformed dose per week, or second-order polynomial (i.e., dose and dose^2^). In the event that a dose-response relationship does not exist, we will compare each of the two intervention groups (low- and high-dose exercise) to the control arm separately. Using a two-sided t-test we will have 80% power to detect a difference in of 32 units for sICAM-1 and 112 units for sVCAM-1, utilizing the sequential testing procedure of Benjamini and Hochberg to protect the family-wise error rate.[155]

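### The fallback pairwise t-tests have about 62–63% power at best, not 80%, for differences of 32 (sICAM-1) and 112 (sVCAM-1) units

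*Protocol*

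**What the plan says.** All the relevant text is in the protocol, Study Procedures, Statistical Analysis, Primary Outcomes.

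- Sample size: "We will randomize 13 participants to each of the three study arms". Allowing for dropout, the aim is 10 completers in each arm.
- Variability: "The standard deviation of sICAM-1 and sVCAM-1 are 30 and 103 units, respectively".
- Main analysis: a linear dose trend. The assumed falls from control are 22 (low dose) and 44 (high dose) units for sICAM-1, and 74 and 148 for sVCAM-1. The power stated for this trend analysis is: "30 subjects provide 80% power for two, two-sided 0.025 tests".
- Fallback when there is no dose-response: "we will compare each of the two intervention groups (low- and high-dose exercise) to the control arm separately".
- Sensitivity claimed for the fallback: "Using a two-sided t-test we will have 80% power to detect a difference in of 32 units for sICAM-1 and 112 units for sVCAM-1". The same sentence promises a sequential multiplicity correction but does not define the family of comparisons.

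The fallback sentence gives no alpha of its own. It offers no sample size or SD other than those already stated.

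**The concern.** Differences of 32 and 112 units are a little over one SD (32/30 = 1.07 and 112/103 = 1.09). Ten per group is too few for 80% power at an effect of that size, even before the multiplicity correction that the same sentence promises.

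The sentence describes what the trial can see on its primary biomarkers if the trend analysis fails. A reader who takes it at face value would think that a true 32-unit sICAM-1 effect is missed one time in five. At 0.05 it is missed 38% of the time (1 − 0.617), and at 0.025 about half the time.

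The figure also falls close to a threshold that matters. The protocol treats a 30-unit fall in sICAM-1 as clinically significant, so 80% power at 32 units implies that the fallback can nearly detect it. Power at 30 units is 56% at 0.05. Because the study is meant to inform a phase III trial, overstated sensitivity could affect how a null comparison with control is read.

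**Working it through.** **Inputs** (all from Primary Outcomes): n = 10 completers per arm; σ = 30 (sICAM-1) and 103 (sVCAM-1); two-sided t-test; Δ = 32 and 112. No alpha is given for the fallback, so I take 0.05 (no correction), 0.025 (strictest step for two tests) and 0.0125 (strictest step if all four comparisons form one family).

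**Formula.** Power = P(T′ > t at 1 − α/2), where T′ is non-central t with noncentrality δ = Δ / (σ√(2/n)). The opposite tail is negligible. For a two-arm comparison df = 2n − 2 = 18.

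**Step 1: reproduce the trend claim.** For three equally spaced, equal-sized arms the trend test has δ = (high − control) / (σ√(2/n)). With df = 28 and two-sided 0.025 the critical value is 2.368.

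- sICAM-1: δ = 44 / (30 × 0.4472) = 3.280, power 81.3%.
- sVCAM-1: δ = 148 / (103 × 0.4472) = 3.213, power 79.6%.

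This agrees with the stated 80%, so the protocol does use n = 10 per arm and these SDs as the error SDs.

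**Step 2: the fallback claim with the same inputs.**

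- sICAM-1: δ = 32 / (30 × 0.4472) = 2.385.
- sVCAM-1: δ = 112 / (103 × 0.4472) = 2.431.

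| Two-sided alpha | Power at 32 (sICAM-1) | Power at 112 (sVCAM-1) |
|---|---|---|
| 0.05 | 61.7% | 63.3% |
| 0.025 | 49.1% | 50.8% |
| 0.0125 | 37.6% | 39.2% |

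**Step 3: differences that do have 80% power, 10 per arm.**

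| Two-sided alpha | Standardised difference | sICAM-1 (× 30) | sVCAM-1 (× 103) |
|---|---|---|---|
| 0.05 | 1.325 | 39.7 | 136.5 |
| 0.025 | 1.484 | 44.5 | 152.9 |
| 0.0125 | 1.638 | 49.1 | 168.7 |

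**Step 4: sample size needed for 32 and 112 units.** At 0.05, 15 per arm gives 80.5% and 82.0%. At 0.025, 19 (sICAM-1) and 18 (sVCAM-1) per arm are needed.

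**Step 5: could another reading give 80%?** Power is shown as sICAM-1 / sVCAM-1.

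| Reading | Power | Fits the text? |
|---|---|---|
| 10 per arm, error df pooled over three arms, 0.05 | 63.3% / 65.0% | Nearly |
| 10 per arm, normal approximation, 0.05 | 66.5% / 68.1% | No, a t-test is named |
| 10 per arm, one-sided 0.05 | 74.2% / 75.6% | No, two-sided is stated |
| All 13 per arm, t-test, 0.05 | 74.2% / 75.8% | Only with no dropout and no correction |
| All 13 per arm, normal approximation, 0.05 | 77.6% / 79.2% | No, for all these reasons |
| 20 pooled exercisers v 10 controls, 0.05 | 75.8% / 77.3% | No, arms are compared separately |
| 26 pooled exercisers v 13 controls, 0.025 | 78.6% / 80.2% | No, same reason |
| 15 per arm, 0.05 | 80.5% / 82.0% | No, 10 per arm is planned |

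The 15-per-arm result would arise if 30 completers were divided into two groups rather than three. That is a guess at the cause; the protocol does not say.

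With 10 per arm, 80% power at 32 and 112 units would need SDs of about 24 and 85 at 0.05. The protocol gives no such values.

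**Step 6: power at the effects the protocol assumes, 10 per arm.**

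- Low dose (22 / 74 units): 34% / 33% at 0.05.
- High dose (44 / 148 units): 87% / 86% at 0.05, and 79% / 77% at 0.025.

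**The case against.** The arithmetic is hard to dispute, but its importance can be.

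- **The sample size does not rest on this sentence.** It rests on the trend test, whose power reproduces. The fallback is conditional, and correcting its figure changes no test, endpoint or participant number in a 39-person pilot whose stated purpose is feasibility, safety and effect-size estimates. This stands and limits the consequence, but it does not make the figure right.
- **The fallback is not uniformly weak.** At the assumed high-dose effects it has 87% and 86% power at 0.05, and nearly 80% at 0.025. This also stands. The shortfall concerns the two stated differences and, more so, effects of low-dose size. The protocol never claims 80% power for 22 or 74 units; those values belong to the linear hypothesis that the fallback sets aside.
- **A sequential procedure is not a fixed stricter alpha.** With a two-test step-up, both comparisons reject if the larger p-value is at or below 0.05. If both arms truly differ from control by 32 units, simulation gives about 57% power per comparison for sICAM-1, between the fixed-alpha figures of 49% and 62%. The 0.0125 row needs a four-test family that the protocol does not define, so it is a lower bound. None of this approaches 80%.
- **Slightly better retention might help.** The section on limits of assumptions expects 80% completion, but 13 × 0.80 = 10.4 per arm, essentially the same n.

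**Conclusion.** The stated 80% power is wrong. From the protocol's own sample size and SDs, power for 32 and 112 units is 62% and 63% at an uncorrected two-sided 0.05, which is 17 to 18 percentage points short. That is the favourable end, because the promised multiplicity procedure can only hold or lower the effective alpha; at 0.025 power is 49% and 51%. The differences with 80% power are 39.7 and 136.5 units at 0.05, or 44.5 and 152.9 at 0.025.

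This assumes 10 completers per arm, equal SDs of 30 and 103 across arms, and separate two-sample t-tests, all as the protocol states. Only the alpha had to be assumed, and no value of 0.05 or below rescues the claim. The primary trend analysis and the total of 39 are not affected.

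**What to change.** In the fallback sentence, replace 32 and 112 with about 40 and 137 units if the statement refers to a single uncorrected two-sided 0.05 test, or with about 45 and 153 units at 0.025. State the alpha, the 10 completers per arm and the SDs beside the figures, and say which comparisons form the family for the sequential procedure.

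It would help, though the correction does not depend on it, to say that the low-dose comparison with control will be read mainly through its estimate and confidence interval, since power for effects of the assumed low-dose size is about one-third.

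The cost is two restated numbers and one alpha. Design, sample size and tests stay as they are, and the stated sensitivity becomes less favourable. Keeping 32 and 112 instead would take 15 completers per arm at 0.05. At the planned 10-in-13 completion that means 15 × 13/10 = 19.5, so 20 randomised per arm and 60 in total, which is hard to justify for a contingent analysis in a pilot.

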**Secondary Outcomes**

The sample size of the COURAGE trial is sufficient to explore the dose-response effects of exercise on VAT and fasting insulin. In the STRRIDE study, changes in VAT among the control, low-dose exercise, and high-dose exercise groups were +8.6%, +1.7%, and –6.9%, respectively.[106-108] Using these point-estimates and a standard deviation of ±17%, we will have 80% power to test the hypothesis of a linear dose-response relationship between exercise and VAT across the three study groups with a type-I error rate of 0.05. In the STRRIDE study, changes in fasting insulin among the control, low-dose exercise, and high-dose exercise groups were +1.1 *μ*U/mL, –0.5 *μ*U/mL, and –0.9 *μ*U/mL, respectively.[114] Using these point-estimates and a standard deviation of ±0.7 *μ*U/mL, we will have ≥80% power to test the hypothesis of a linear dose-response relationship between exercise and fasting insulin across the three study groups with a type-I error rate of 0.05. For our exploratory correlational analysis (i.e., exploratory aim), we will have 80% power to detect a correlation of *≥*0.40 between the exercise-induced improvements in VAT and the exercise-induced improvements in fasting insulin.

For the outcomes of VAT and fasting insulin, we will use a linear mixed-effects regression model to compare the change in outcome levels for each treatment group while simultaneously controlling for other variables identified to influence VAT and fasting insulin (i.e., a multivariable adjusted linear mixed model). Potential confounders (e.g., changes in diet, sleep, and smoking) will be screened using univariate models; those that appear to be associated with the outcome will be entered sequentially in multivariate models. We will fit models including dose as a linear term, and assess model fit using standard methods. Alternatives to a linear dose trend include transformations of dose such as average actual dose, log-transformed dose per week, or second-order polynomial (i.e., dose and dose^2^). In the event that a dose-response relationship does not exist, we will compare each of the two intervention groups (low- and high-dose exercise) to the control arm separately. In our exploratory correlational analyses, we will calculate Pearson’s product-moment correlation coefficient (*r*) to quantify the strength of the relationship between the exercise-induced improvements in VAT and the exercise-induced improvements in fasting insulin.

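### The 80% power stated for the linear trend in visceral fat is about 50% on the protocol's own means, SD and 10 completers per arm

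*Protocol*

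**What the plan says.** The Secondary Outcomes part of the Statistical Analysis section opens with the claim that "The sample size of the COURAGE trial is sufficient to explore the dose-response effects of exercise on VAT and fasting insulin". For VAT it takes its effect sizes from an earlier dose-response exercise trial, in which "changes in VAT among the control, low-dose exercise, and high-dose exercise groups were +8.6%, +1.7%, and –6.9%, respectively". It then states: "Using these point-estimates and a standard deviation of ±17%, we will have 80% power to test the hypothesis of a linear dose-response relationship". The sentence specifies a "linear dose-response relationship between exercise and VAT across the three study groups with a type-I error rate of 0.05". Whether the test is one- or two-sided is not given.

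No separate sample size is given for VAT, so the trial's own applies. The Primary Outcomes part sets it: "We will randomize 13 participants to each of the three study arms", in order "to achieve 10 per group who complete the study (76% completion rate"). The planned analysis enters dose linearly: "We will fit models including dose as a linear term, and assess model fit using standard methods".

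**The concern.** The sentence names its inputs, so the 80% can be checked directly, and it looked too high. A 15.5-point difference between the extreme arms is less than one SD (15.5/17 = 0.91), with only 10 completers per arm. The primary biomarkers have a larger standardised difference (44/30 = 1.47 for sICAM-1), and the protocol claims 80% for those, although at the stricter level of 0.025.

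The figure supports the statement that the sample is large enough to study VAT, for which the protocol has a directional secondary hypothesis. If true power is near 50%, a real trend of the assumed size would be missed about half the time. The Secondary Outcomes text also switches to pairwise comparisons with control if no dose-response is found, and a non-significant trend at this power is weak ground for that step. Finally, the trial is meant to supply effect sizes for a phase III trial. A null VAT result believed to carry 80% power could be given too much weight there.

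**Working it through.** **Inputs**

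| Input | Value | Source |
|---|---|---|
| Mean VAT change: control, low, high | +8.6, +1.7, –6.9 points | Secondary Outcomes |
| SD | 17 points | Secondary Outcomes |
| Type I error | 0.05, sidedness not stated | Secondary Outcomes |
| Completers per arm | 10 (13 randomised) | Primary Outcomes |
| Doses | 0, 150, 300 min/week, entered linearly | Objectives; Secondary Outcomes |

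**Formula.** Doses are equally spaced and arms equal, so the linear contrast has weights –1, 0, +1 and the middle arm drops out. The non-centrality is

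δ = |high – control| / (SD × √(2/n)),

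and power comes from the non-central t distribution with 3n – 3 degrees of freedom.

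**The method on the protocol's other power claims.** The primary claim is that "30 subjects provide 80% power for two, two-sided 0.025 tests". With n = 10 per arm and two-sided 0.025:

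- sICAM-1: δ = 44 / (30 × √0.2) = 3.28; power 81%.
- sVCAM-1: δ = 148 / (103 × √0.2) = 3.21; power 79%.

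Both agree with the stated 80%. For fasting insulin at two-sided 0.05, δ = 2.0 / (0.7 × √0.2) = 6.39 and power exceeds 99%, consistent with the stated figure of at least 80%.

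**VAT with the same method**

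- Difference: 8.6 – (–6.9) = 15.5.
- Standard error: 17 × √(2/10) = 7.60.
- δ = 15.5 / 7.60 = 2.04.
- Two-sided power at 0.05, 27 df: 50%. The normal approximation gives 53%. Simulating the regression slope test 100,000 times gives 50%.

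**More favourable readings of the stated inputs**

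| Reading | Power |
|---|---|
| Two-sided, 10 per arm | 50% |
| Two-sided, all 13 per arm | 62% |
| One-sided, 10 per arm | 63% |
| One-sided, all 13 per arm | 74% |

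Alternative tests do worse. The omnibus F test gives 39% (10 per arm) or 50% (13 per arm), and log-transformed dose with 10 per arm gives 42%.

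**What 80% would require (two-sided 0.05)**

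- At SD 17 and a 15.5-point difference: 20 completers per arm (power 81%; 19 per arm gives 79%).
- At 10 per arm and a 15.5-point difference: an SD of about 11.9.
- At SD 17: a difference of 22.1 points with 10 per arm, or 19.2 with 13 per arm.

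**The case against.** The planned analysis is a covariate-adjusted mixed model, not a bare contrast, and the protocol does not say exactly what the 17% is the SD of. Some assumptions do bring the power to about 80%:

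- **Covariates.** They would have to explain about 51% of the variance of change with 10 per arm (1 – (11.9/17)² = 0.51). With all 39 analysed, about 35% would do (the SD needed is 13.7, and 1 – (13.7/17)² = 0.35).
- **A cross-sectional SD.** If 17 is the SD of a single measurement and the baseline-to-six-month correlation is 0.75, the SD of change is 17 × √(2 × 0.25) = 12.0. Power with 10 per arm is then 79%.

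So 80% is not impossible, but the protocol states neither assumption. It attributes the 80% to the listed point estimates and the 17% SD, and it sets that SD beside mean changes. The covariates are only examples of candidates to be screened later. The primary power claim reproduces without any such allowance.

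It can also be said that VAT is secondary, that the sample was sized on the biomarkers, and that the text claims only enough participants to explore the effect. That is correct and limits the consequences: the primary calculation stands and enrolment does not depend on the VAT figure. The protocol also does not say that a null VAT result would be taken as proof of no effect. None of this makes the stated number right, because the sentence is a quantitative claim about testing a hypothesis.

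**Conclusion.** The 80% is wrong as written. The protocol's own means, SD and planned completers give about 50% power for the VAT trend at two-sided 0.05, and 62% if nobody drops out. No combination of the stated inputs exceeds 74–75%, the one-sided result with all 39 analysed (74% by non-central t, 75% by normal approximation).

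This rests on reading 17% as the SD of the percentage change, on equal arms, and on equally spaced doses. It takes the test as two-sided by analogy with the primary tests; the one-sided results above show that this choice does not decide the matter. The error is confined to VAT. The power statements for the primary biomarkers and fasting insulin are consistent with the same formula.

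**What to change.** In Secondary Outcomes, replace the VAT power sentence with text along these lines: *With 10 completers per arm, an SD of change of 17 percentage points and a two-sided type I error of 0.05, power for the cited linear trend is about 50%; 80% power is reached for a control-to-high-dose difference of about 22 percentage points.* The statement that the sample is sufficient should be withdrawn for VAT or qualified by this figure.

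If the 80% relied on a smaller residual SD, the protocol should instead state the N, the sidedness, what the SD refers to, and the covariate or pre-post correlation assumption used, with its justification.

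Reporting the VAT trend mainly as an estimate with a 95% confidence interval would suit a feasibility trial with this precision, but the correction does not depend on it. The cost is a few sentences of text, with no change to enrolment, procedures or the primary analysis.

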***3.*** ***Confidentiality***

How will confidentiality of data be maintained? Check all that apply.

Paper-based records will be kept in a secure location and only be accessible to personnel involved in the study.

Computer-based files will only be made available to personnel involved in the study through the use of access privileges and passwords.

Prior to access to any study-related information, personnel will be required to sign statements agreeing to protect the security and confidentiality of identifiable information.

Whenever feasible, identifiers will be removed from study-related information.

A Certificate of Confidentiality will be obtained, because the research could place the subject at risk of criminal or civil liability or cause damage to the subject’s financial standing, employability, or liability.

A waiver of documentation of consent is being requested, because the only link between the subject and the study would be the consent document and the primary risk is a breach of confidentiality. (This is not an option for FDA-regulated research.)

Precautions are in place to ensure the data is secure by using passwords and encryption, because the research involves web-based surveys.

Audio and/or video recordings will be transcribed and then destroyed to eliminate audible identification of subjects.

Other *(specify):*

Data will be de-identified upon completion of all study activities, including any resulting publications. Data will be kept confidential throughout the course of the project by ensuring that the staff in position of or with access to the data will have completed all appropriate training and will keep paper files in a locked cabinet and electronic files will be in password protected files behind a firewall. Data will be physically stored in a locked file cabinet in an office at Penn. No data will become part of the patient’s permanent record. The data will be kept for a minimum of five years after study completion.

***4. Privacy***

We will keep all patient databases private. All measurements will be taken in a private room. Participants will be told in advance that if they are selected into one of the exercise groups, they may be in a group setting with other CC survivors and it will not be possible to conceal the fact that they are CC survivors from other participants. For example, after randomization if two participants opt to attend their supervised exercise sessions at the same time. We will remind the participants to respect privacy by not revealing the identity of their fellow group members without permission to do so.

